## Abstract

Previous studies in primary care settings showed that brief advice prescribing physical activity for inactive patients could be an effective way to promote physical activity. Park prescription interventions confer health benefits associated with exposure to nature and increased physical activity by recommending park use specifically to increase physical activity in parks. The purpose of this trial is to evaluate the effectiveness of a park prescription intervention for increasing time spent in moderate-to-vigorous physical activity (MVPA) assessed by accelerometry. Middle-aged Singaporeans who were insufficiently active and who met health screening criteria were recruited via existing community health screening programs and allocated to one of two groups. Intervention participants received a prescription of physical activity in parks, an information pack, access to a weekly group exercise program in parks and telephone counselling (*n* = 80). Control participants received physical activity materials (*n* = 80). The primary outcome (mean difference between both groups in time spent in MVPA minutes per week measured by accelerometer) will be assessed at six months. Secondary outcomes include self-reported health behaviors, self-reported mental wellbeing and objectively-measured physical health. This is the first randomized controlled trial investigating the effectiveness of a park prescription intervention for increasing health-enhancing MVPA.

## 1. Introduction

Physical inactivity is a major contributing factor to increases in non-communicable diseases globally [1]. In Asia, non-communicable disease prevention is a priority for governments to act upon [2]. The Singapore government has sustained efforts to prevent non-communicable diseases and recently declared diabetes prevention a national priority [3,4,5,6].

The prevalence of adequate physical activity engagement according to international guidelines is 76.7% globally and 85.2% in South-East Asia [7]. The population-based 2012 Singapore Health study found that 73.8% of all adults and 70% of adults aged 40–59 years performed sufficient total physical activity [8]. Yet, the same Singaporean study and a separate Taiwanese study found that middle-aged people living in these countries exercise the least [8,9]. Community health screening programs for residents over the age of 40 are freely available throughout Singapore. Results of these screenings have showed that a large proportion of this population is not sufficiently physically active. Therefore, these community health screenings present an opportunity to promote physical activity to this portion of the Singaporean population. Reviews have identified evidence of health benefits associated with exposure to parks and other green space including improved mental health, reduced prevalence of type II diabetes and reduced mortality [10,11,12]. Since most of the available research is from cross-section studies which only provide evidence of associations, it is not possible to infer causal relationships between exposure to parks and health outcomes. A systematic review of the impact of interventions to promote physical activity in urban green space concluded that they appear promising but ‘robust evaluations of such interventions are urgently required’ [13]. Consequently, a need exists to implement stronger studies which support causal arguments for exposure to parks improving health.

The Park Prescription concept emerged from collaboration between the U.S. Centers for Disease Control and Prevention and the National Recreation and Parks Association. In 2013 ‘Park Prescriptions’ were defined as ‘Programs designed in collaboration with healthcare providers … to utilize parks, trails and open space for improving … community health’ [14]. This is closely related to the concept of exercise prescription for people who are not sufficiently physically active [15]. Previous studies which examined prescription of physical activity in primary care settings showed that brief written or oral advice prescribing frequency, intensity, time and type of physical activity for inactive patients could increase physical activity levels [16,17].

Singapore offers an opportunity to explore the application of Park Prescription since there are many accessible and well-managed parks on the relatively small island [3]. Whilst there have been recent studies of prescribing physical activity in parks [18,19], to our knowledge this is the first randomized controlled trial (RCT) to examine the effectiveness.

### 1.1. Study Objectives

The primary objective was to investigate the effectiveness of a park prescription intervention to increase time spent in moderate-to-vigorous physical activity (MVPA) assessed by accelerometry. Secondary objectives included the investigation of intervention effectiveness for:improving participants’ total volume of physical activity per week, reflecting average acceleration peroin gravitational units (mg); the amount of light physical activity in minutes per week, the amount of sedentary behavior in hours per week (all assessed via accelerometer);improving participants’ self-reported health behaviors including time spent in parks, physical activity time in parks, recreational physical activity and sedentary behavior;promoting participants’ self-reported mental well-being; and,improving participants’ objectively measured physical health.

## 2. Materials and Methods

The Standard Protocol Items: Recommendations for Intervention Trials (SPIRIT) guidance document for protocols of clinical trials has been used to ensure the content provided in this protocol covers all information that supports the quality of the trial [20].

### 2.1. Study Design

The Park Prescription Trial (PPT) was a parallel group, two-arm, prospective, superiority RCTwith 1:1 allocation ratio to either intervention or control arm. Participants in both arms completed assessments at baseline (V0), 3-month mid-intervention follow-up (V1) and 6-month follow-up at completion of the intervention (V2).

### 2.2. Trial Setting

The PPT was conducted in the community setting in Singapore. Participants were recruited face-to-face or via phone calls and letters to a list of past screening participants. They were recruited at their local community screening program at Khoo Teck Puat Hospital (KTPH) or other community locations organized by KTPH also in the northern area of Singapore or following a health screening of an existing National University of Singapore (NUS) cohort study if their home postal code was also in Singapore’s north. The group exercise component of the intervention was conducted in three regional parks—Woodlands Town Park East, Admiralty Park and Yishun Park—which are near the areas where participants were recruited from. All regional parks in Singapore are well-maintained and these parks have green, landscaped surroundings and shaded areas for the group exercise sessions.

### 2.3. Eligibility Criteria

Subjects who participated in the study met all of these inclusion criteria:Singapore citizen or Permanent Resident;aged 40–65 years;self-reported weekly exercise of <150 min per week;blood pressure of ≤139 mmHG (systolic) over ≤89 mmHG (diastolic);fasting glucose level of ≤6.0 mmol/L;pass the adapted Physical Activity Readiness Questionnaire (PAR-Q) [21];able to write and read in English or Chinese; and,provide written informed consent.

Pregnant women and those with physical disabilities or lower limb disorders were excluded from participation.

The PAR-Q is a self-guided, nine-question screening tool that can quickly identify conditions or risk factors that require further assessment before engaging in physical activity [21]. For the current trial, we used an adapted version of the PAR-Q (referred to as PAR-Q2), which also included an additional section to formally assess subjects’ age, whether they have physical disabilities or lower limb disorders and the time they spend exercising on a weekly basis.

### 2.4. Intervention

#### 2.4.1. Group 1—Park Prescription Trial (PPT) Intervention

The participants in this group received brief counselling on physical activity along with a park prescription sheet that highlights the importance of engaging in at least 150 min of physical activity per week and the possibility of engaging in physical activity in a park in their neighborhood. The park prescription sheet also includes information on frequency, intensity, time and location of activities and signature fields for the participant and prescriber to sign once they agreed on the prescription. They also received a sheet which was used to plan their weekly physical activity and two information brochures about parks in their neighborhood. Half-way through the trial a trained study team member provided a brief counselling phone call. In addition, they were invited to join in a weekly one-hour outdoor structured and supervised physical activity program in the park for a period of six months. Each one-hour session comprised moderate intensity aerobic activity and strength and balance exercises. The structured physical activity program took place in public parks located in the participants’ neighborhood. The sessions utilized different areas and features of the parks, including walking trails and open spaces, to maximize participants’ exposure to greenery. In the event of inclement weather, the sessions would be held instead at predetermined sheltered indoor locations adjacent to the parks, which had already been booked for that purpose. Participants chose to attend either a session on Tuesday between 7.30–8.30 p.m., or a Sunday morning session mostly between 8.00–9.00 a.m.

The five components of the intervention are described further in Table 1. Protocols were developed to ensure consistent implementation by the study team. All participants were enrolled for approximately six months. Adherence to all components was monitored and recorded by study staff and the proportion that adhered to each component was recorded.

#### 2.4.2. Group 2—Control

Participants in this group continued with their daily routine. They were not given any park prescription or invited to participate in the weekly program in the park. However, they received standard physical activity promotion materials, which were existing publications by the Health Promotion Board, Singapore. In addition, they received all the information materials after Group 1 completed the study and they were also invited to join ongoing exercise classes upon study completion.

### 2.5. Outcomes

Table 2 summarizes the primary and secondary outcomes, the instruments used and the measurement time points.

#### 2.5.1. Primary Outcome

The primary outcome for the study is the mean difference between the intervention group and the control group in time spent in MVPA (minutes per week) objectively quantified via an accelerometer (ActiGraph wGT3X-BT) at the six-month follow-up. This outcome was chosen since it is accepted as an objective physical activity measure that is valid, reliable and practical for use in community trials.

#### 2.5.2. Secondary Outcomes

Secondary outcome measures are defined as the differences between the mean values in the intervention and the control groups at six months follow-up in health behaviors, mental wellbeing and physical health.

Measures for health behaviors related to physical activity include the total volume of activity reflecting average acceleration in gravitational units (mg), time spent in light intensity physical activity and sedentary activity measured by accelerometer, as well as recreational activity time per week, subjectively-measured total MVPA time per week and sedentary time per week assessed by self-administered questionnaire. The physical activity questions come from the previously validated WHO Global Physical Activity Questionnaire [22]. The questions on sedentary time come from the validated International Physical Activity Questionnaire [23]. Self-reported time spent in parks in the past month and time spent doing physical activity in parks in the past month were also included in the self-administered questionnaire at baseline, three months and six months follow-up.

The secondary outcome measures for mental wellbeing include the difference in self-reported quality of life and mental wellbeing between the intervention group and the control group at six months follow-up. This was measured by previously validated survey questions including the general health item from the SF-12, K-10, WHO5 and the WHOQOL-BREF [24,25,26,27]. The physical health measures are objectively-measured Body Mass Index (BMI), fasting blood glucose levels as well as systolic and diastolic blood pressure, as assessed prior to baseline and during the health screening visit at six months follow-up.

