### 2.10. Data Collection and Analysis

#### 2.10.1. Data Collection

Table 2 summarizes data collection measures and instruments at each of the three measurement time points. The types of measures are also described in detail under Section 2.5 Outcomes and this section provides information on the procedures used to ensure quality of data collection and completeness of follow-up.

At baseline, secondary outcome measures of physical health including blood chemistry (blood lipids, fasting blood glucose), blood pressure (systolic and diastolic) and anthropometry (height and weight) had been collected prior to enrolment in the trial as part of existing health screenings or as part of data collection for the existing NUS cohort study. The data at these health screenings are collected by nurses who are trained in standard procedures for collecting the anthropometric data accurately and reliably and taking blood safely. The questionnaire, which combined items from several validated questionnaires, was piloted with a small sample who were of the same age range as study participants. Pilot participants were from the National University Hospital clinics. The pilot was used to see that the time to completion was acceptable and all questions were understood. Staff were also instructed to check for missing data and plausibility. To increase participant retention, participants’ contact details were collected at baseline for follow-up.

At the three-month follow-up, self-administered questionnaires were mailed to participants for completion with a stamped, addressed return envelope as well as a letter thanking them for their participation and encouraging them to return the questionnaire within one week. If the surveys were not returned, participants received reminder text messages and if necessary follow-up phone calls. Participants who did not complete the survey at three months were still followed up at six months.

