#### 2.10.3. Statistical Analysis

For demographic variables of the intervention and control groups at baseline, descriptive statistics will be presented using mean and standard deviation for variables that are normally distributed and median and interquartile range for skewed continuous variables and proportion for categorical variables. Table 3 provides an overview of all primary and secondary outcome measures, their definitions and the methods to be used for evaluating the respective hypotheses.

For the continuous primary outcome of MVPA as well as continuous secondary outcomes based on health behavior, mental health and physical health measures at the six-month follow-up, the mean difference between the intervention and the control groups will first be evaluated using t-tests. Further adjustment for respective baseline values of the outcome variables (where available) of the individual will be made via multiple linear regression analysis. For accelerometer related outcomes where no baseline value is available, adjustment for total self-reported MVPA of the individual will be made via multiple linear regression analysis. For categorical outcomes at 6-months (e.g., depression/anxiety levels from K10) logistic regression will be conducted adjusting for the same covariates.

Subgroup analysis based on the report of engagement in physical activity in parks will be performed to investigate the effect of the intervention on the primary and secondary outcomes.

Up-to-date versions of R (Auckland, New Zealand) and STATA (Texas, TX, USA) will be used to conduct the analysis. All evaluations will be made based on intention to treat, assuming a two-sided test at the 5% level of significance. Effect sizes and 95% confidence intervals will also be reported for the respective outcome measures.

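### Self-reported activity, sitting time and park use are collected from both arms at three months, but between-arm efficacy results are specified only at six months

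*Protocol article*

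**What the plan says.** **Collection.** Section 2.1 has both arms assessed at V0, V1 and V2. Table 2 marks the GPAQ, IPAQ sitting time and park-use rows at all three points. For the two park items, Section 2.5.2 says they "were also included in the self-administered questionnaire at baseline, three months and six months follow-up". Section 2.10.1 describes the V1 procedure: "At the three-month follow-up, self-administered questionnaires were mailed to participants for completion". Reminder texts and, if needed, phone calls follow when forms are not returned. People who miss V1 are still approached at V2.

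**Endpoints.** Section 2.5.2: "Secondary outcome measures are defined as the differences between the mean values in the intervention and the control groups at six months follow-up".

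**Analysis.** Section 2.10.3 applies t-tests, then baseline-adjusted linear regression, to the primary outcome and to "continuous secondary outcomes based on health behavior, mental health and physical health measures at the six-month follow-up". Logistic regression for categorical outcomes is also at six months. The section presents Table 3 as the overview of all primary and secondary outcomes and their methods, and the Table 3 hypotheses are dated to six months.

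**Related statements.** Section 2.6 allows for 20% drop-out. The Discussion relies on intention to treat to reduce bias from loss to follow-up. It also says that the six-month follow-up will show whether changes are maintained.

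**The concern.** Five secondary outcomes have two post-baseline measurements in each arm: total self-reported MVPA, recreational MVPA, sitting time, time in parks and active time in parks. Followed as written, the analysis uses one of the two. This has two consequences.

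1. **Missing data.** A regression of V2 on arm and V0 leaves out anyone without V2. It is valid if V2 missingness depends only on arm and the baseline value. If people whose activity had not improved by three months are more likely to leave, that condition fails. The V1 answer that would help account for it has been collected but is not used.
2. **Time course.** V2 falls at the end of the intervention, and the group exercise runs over the whole six months (Table 1). A single comparison at V2 cannot show whether an early change held or faded. The V1-to-V2 comparison is the only between-arm evidence available on that, and none is specified.

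**Working it through.** **Tracing the V1 items in Table 2**

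| V1 item | Arms | Other visits | Stated use of the V1 value |
|---|---|---|---|
| GPAQ physical activity | both | V0, V2 | no dated efficacy analysis |
| IPAQ sitting time | both | V0, V2 | no dated efficacy analysis |
| Park use | both | V0, V2 | no dated efficacy analysis; the park-activity subgroup names no visit |
| Motivation (BREQ-2) | intervention | none | fits the process evaluation |
| Satisfaction with prescription sheet and brochure | intervention | none | fits the process evaluation |
| Satisfaction with planning sheet | intervention | none | fits the process evaluation |

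The gap is confined to the first three rows.

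**The plan's own sample size.** With a difference of 30, SD 60, two-sided alpha 0.05 and 80% power (standardised difference 30/60 = 0.5), the two-sample t-test needs 63.77, so 64 per arm. Then 64/0.8 = 80 per arm. The stated figures reproduce, and this point does not touch them: the primary outcome is accelerometer MVPA, measured at V2 only.

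**Precision gain for the V2 contrast**

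From the document: 80 randomised and 64 completing V2 per arm, so 80 − 64 = 16 without V2. Assumed, because the document gives no figure: equal correlation r between any two visits (compound symmetry), r from 0.5 to 0.7; V1 available for all 64 completers and, as a best case, for all 16 non-responders.

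Step 1. Partial correlation of V1 and V2 given V0: ρ = (r − r²)/(1 − r²) = r/(1 + r).

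Step 2. With V1 on 80 and V2 on 64, effective n = 1 / [ρ²/80 + (1 − ρ²)/64].

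| r | ρ | ρ² | effective n per arm |
|---|---|---|---|
| 0.5 | 0.333 | 0.111 | 65.5 |
| 0.6 | 0.375 | 0.141 | 65.9 |
| 0.7 | 0.412 | 0.170 | 66.2 |

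Step 3. The standard error shrinks by the factor √(64/65.5) = 0.988 to √(64/66.2) = 0.983, that is, by 1 to 2%.

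Step 4. If only half of the 16 returned V1, replace 80 by 72. Effective n is then 64.8 at r = 0.5 and 65.2 at r = 0.7.

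**The V1-V2 average, for comparison.** Adjusted for V0, its variance relative to V2 alone is ((1 + r)/2 − r²)/(1 − r²) = 0.667, 0.688 and 0.706 for r = 0.5, 0.6 and 0.7. That is a 29-33% reduction, but for a different quantity from the six-month endpoint.

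**The case against.** **Nothing here is contradictory.** Fixing the endpoint at the end of the intervention while taking an interim measure is a coherent design. The six-month timing is consistent throughout, and one time point limits multiplicity across many secondary outcomes. An article also commonly leaves supporting analyses to the full protocol or analysis plan, which are not shown. Most of this stands, and it is why the point is only a suggested improvement. It does not remove the point, because the article names the method for these outcomes and dates it to six months. An analysis plan that followed it would leave the three-month responses out.

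**The precision gain may be smaller still.** V2 has mostly home delivery, a health screening and the final cash payment behind it, while V1 is a mailed form. The number with V1 but no V2 could be small. This stands, and the figures above are upper limits for the assumed correlations.

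**Stronger readings that the documents do not support**
- A reader might infer that the three-month assessment feeds no result. It is the only time point for BREQ-2 and for satisfaction with the sheets and brochure, which match the process evaluation announced in the Discussion.
- A reader might infer that every analysis is limited to six months. The subgroup analysis by reported park activity states no visit and could draw on V1.
- A reader might take the 29-33% variance reduction as the loss on the planned endpoint. It belongs to the V1-V2 average, which answers a different question.

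**Conclusion.** The point holds in a limited form. For self-reported activity, sitting time and park use, the article specifies no between-arm result for the three-month values, and participants with V1 but no V2 contribute nothing to these outcomes. The primary outcome, the sample size and the process evaluation are untouched.

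The precision gain is minor: at most about 1.5 to 2.2 extra effective participants per arm (64 to 65.5-66.2), under compound symmetry with r = 0.5-0.7 and full V1 return among V2 non-responders. The case for change rests on the other two gains. A model with V1 as a response stays valid when V2 missingness depends on V1, provided the data are missing at random and the model is adequate; it does not protect against drop-out that depends on unobserved values. It also gives the only V1-to-V2 evidence on whether early changes hold. That bears on the Discussion's statement about maintenance, but only within the intervention period, since V2 falls at its end.

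**What to change.** For the five self-reported outcomes only (total and recreational MVPA from GPAQ, IPAQ sitting time, time in parks, active time in parks), replace the six-month-only regression with one repeated-measures model per outcome. V1 and V2 are the responses; arm, visit, arm-by-visit and the V0 value are the terms; the two responses from a participant are allowed to correlate. Keep the V2 between-arm contrast as the endpoint. Report the V1 contrast and the between-arm difference in V1-to-V2 change as supporting results, and label them so before the data are analysed. Leave the accelerometer outcomes, mental wellbeing and physical health analyses as they are, since none of these is measured at V1.

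The cost is a few lines of analysis wording and five models on data already scheduled for collection, with no added visits or participants. The downside is a few more supporting contrasts to report.
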